### Criteria for suspension

The patient can cancel the study at any time without having to provide reasons. Patients can be taken out of the study prematurely if there are non-tolerable side effects that need to be treated. However, the study follows an intention to treat--ambition which means that data collected until then will be used for analysis and attempts will be made to still get a follow-up even if the person has not completed.

### Rejection log

The investigator shall document all patients who have been on screening visits, which have been included and not, and why they have not been included in the study.

## 9. Treatment

Experimental drug is degarelix (Firmagon) 240 mg (at the same time 2 injections subcutaneous à 120 mg), follow-up after 2 weeks and 10 weeks.

Placebo substance is corresponding volume sodium chloride solution (2 injections subcutaneous), same follow-up time.

### Description of the experimental drug

Powder and injection fluid, solution 120 mg. Manufacturer Ferring. The dose of 240 mg that we use in the study is the same as recommended as the starting dose in FASS in prostate cancer and the same as evaluated in the above stated Phase III studies. In addition to active substance, the drug also contains mannitol (facilitates, among other things, the transport of active substance over the blood-brain barrier).

### Packing, marking, and handling of the experimental drug

The drugs are purchased through Apoteket, ApoEx, to CASM and stored there in one for the purpose intended locked cabinets (temperature < 25°C) together with identification and randomization keys. The solution is not prepared in advance but in direct connection to administration. If it is waiting, prepared syringes are stored for up to two hours in the same cabinet, waiting will be longer than that, a new syringe will be prepared. We have discussed with Apoteket's clinical trials unit, karolinska university hospital pharmacy hospital pharmacy, about cooperation, but given the short shelf life after preparation and given the transport times between their unit in Solna and our reception in Huddinge, the common assessment is that it is better to have an unblinded research nurse in place instead, at CASM, Huddinge.

### How treatment is assigned

The randomization is done in advance according to the model "adaptive biased coin--/ urn-- design" in balanced blocks, which is the most optimal way with respect to the number of participants and practical conditions in general. Opaque sealed envelopes, sequentially numbered and containing information about placebo/degarelix are located in a box in the same locked cabinet. When a new subject is to be injected, the research nurse takes the top envelope in the pile provides placebo or degarelix according to instructions in the letter. Since both interviewers and subjects should be blinded, the info is kept secret for the subject. The letter paper also writes the patient's reserve number. The letter is put back in the same place. This will be our randomization key.

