## 7. Design

### Overview design

The study is a investigator-initiated clinical trial, phase 2, Therapeutic exploratory. The design is a double-blind randomized placebo-controlled, parallel groups.

The study design is in accordance with the Helsinki Declaration guidelines. Gold standard for primary prevention of sexual abuse in children with pharmacological treatment of people with pedophilia is lacking, which is why comparison between active substance occurs against placebo (sodium chloride solution).

Randomization is done in advance according to the model "adaptive biased coin-urn--design", balanced in blocks, which is the most optimal way in terms of the number of participants. Randomization takes place in advance. Opaque sealed envelopes, as many as the number of subjects in the RCT (N=60), sequentially numbered, contain information about placebo/degarelix located in the same locked cabinet as the trial drug. When a new subject is to be injected, the research nurse takes the top envelope in the pile and provides placebo or degarelix according to instructions in the letter. When baccused interviewers and subjects should be blinded so secret is kept secret for the subject. The letter also has room to document the subject's reserve number. This establishes continuous randomization key. It is defended in the same locked cupboard.

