The research participants are completely anonymous to the investigators. This is in order to increase the likelihood that participants are honest in their answers; the shame becomes less towards the interviewer if they are anonymous and they do not have the obligation to notify the Social Service Act for the interviewer to take into account in their answers. The anonymisation is carried out in practice by giving the research participant an anonymous medical chart (reserve number) by the research nurse who is the one with the identification key. The investigator and the researchers are also blinded in terms of what substance the research person has been injected. Only the research nurse has knowledge of this. She has registered this in the same identification key. The key is in paper format and is stored in a binder marked "PRIOTAB" together with the study drugs in a for purpose intended, locked refrigerator on CASM. Even the researchers are blind to what substance they received. The supply of medicines takes place at the end of the visiting period. Evaluation takes place on weeks and 10 weeks later. The researchers are therefore in the hospital on three occasions. The third investigative moment without an MRI investigation.

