#### Study size

The size of the study is motivated by the secondary objectives and not the primary. Ass [name] recommendation on study size for the secondary objectives is, based on study design in general, N=30 in each treatment arm in PRIOTAB-RCT, (N=60), as well as equal number of controls for comparison in PRIOTAB-- CC.

Konfidentiellt

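### The unblinded nurse reads each allocation before the patient is tied to the sealed envelope, and the balancing method is unclear, so concealment from her is incomplete and the audit trail weak

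*Supplement*

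**What the plan says.** Sections 7 (Overview design) and 9 (How treatment is assigned) describe the same procedure.

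- **Envelopes.** The list is made beforehand. Section 7: "Opaque sealed envelopes, as many as the number of subjects in the RCT (N=60), sequentially numbered". Section 9: "Opaque sealed envelopes, sequentially numbered and containing information about placebo/degarelix are located in a box in the same locked cabinet". The drug and the keys are kept in that cabinet too.
- **Draw.** When a man is due for injection, the research nurse takes the uppermost envelope and gives what the letter states.
- **Link to the patient.** Section 7: "The letter also has room to document the subject's reserve number". Section 9: "The letter paper also writes the patient's reserve number. The letter is put back in the same place". These letters form the randomisation key.
- **Who knows.** On the substance given, section 7 states: "Only the research nurse has knowledge of this". The nurse also issues the reserve numbers and holds the identification key.
- **Method.** Both sections name an adaptive biased-coin/urn design and add that it is balanced in blocks. Section 9: "in balanced blocks, which is the most optimal way with respect to the number of participants and practical conditions in general". Neither gives a block size or says whether it varies. The SAP of June 2019 does not return to the subject.
- **Timing.** In the Visit 1 timetable (section 7, Assessments and procedures), a doctor obtains consent and the nurse registers the man in the morning. Randomisation and dosing come last, at 16:00 to 16:30.

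**The concern.** A sealed envelope protects concealment when the patient is committed to it, in writing, before it is opened. Here the only written link is made on the letter, so it follows the reading of the allocation. The person who makes the link also registers the man, keeps the envelopes and the key, prepares and gives the injection, and knows all previous results. If the list is balanced in blocks, those results let her work out some of the coming assignments, to an extent the protocol does not fix.

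The stake is whether concealment can be demonstrated in a trial of 60 men run from one clinic. The analysis leans on it: the primary test is an unadjusted t-test on change, and the SAP justifies leaving baseline covariates out of the secondary models by the fact of randomisation.

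**Working it through.** The documents give no figure for predictability, so there is none to reproduce.

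**1. How much could be foreseen**

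Inputs from the documents: 60 envelopes (section 7); 30 per arm, hence 1:1 (section 12, Study size); earlier allocations known to the nurse (section 7). Assumptions: the block size, that she knows it, and the parameters of the schemes without blocks.

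In a block of 2m with m per arm, an assignment is certain once one arm is used up. The certain assignments are therefore the run of identical treatments that ends the block. Its expected length is the sum over k = 1 to m of P(last k identical) = 2 × C(2m−k, m) / C(2m, m). The sum is 2m/(m+1), and dividing by 2m gives a share of 1/(m+1).

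- Block of 4: 1 + 1/3 = 1.333; 1.333/4 = 33.3%.
- Block of 6: 1 + 0.4 + 0.1 = 1.5; 1.5/6 = 25%.

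The share guessed correctly, by always naming the arm that is behind, is [m + (4^m / C(2m, m) − 1)/2] / 2m.

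- Block of 4: (2 + (16/6 − 1)/2)/4 = 2.833/4 = 70.8%.
- Block of 6: (3 + (64/20 − 1)/2)/6 = 4.1/6 = 68.3%.

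Simulation for N = 60 agrees (2,000 lists per block size; 3,000 lists for each scheme without blocks).

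| Assumed scheme | Known with certainty | Of 60 | Guessed correctly |
|---|---|---|---|
| Blocks of 2 | 50% | 30 | 75% |
| Blocks of 4 | 33% | 20 | 71% |
| Blocks of 6 | 25% | 15 | 68% |
| Blocks of 10 | 17% | 10 | 65% |
| Blocks of 20 | 9% | 5.5 | 62% |
| One block of 60 | 3% | 1.9 | 57% |
| Urn, starting empty | 2% | 1 | 55% |
| Urn, starting with one ball per arm | 0% | 0 | 55% |
| Biased coin, probability 2/3 | 0% | 0 | 62% |

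Pure chance gives 50% correct guesses. Every scheme is somewhat predictable to a person who knows the history. Whether the amount is slight or large depends on the choice that the protocol leaves open.

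**2. What the records could and could not show**

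| Record | Shows | Does not show |
|---|---|---|
| Numbered envelopes and retained letters (sections 7 and 9) | Use out of order, if the envelope number stays with the letter | When the seal was broken; letters exchanged before a number was written |
| Administration in the reserve-number chart (section 9, Drug accounting) | That the man was dosed | That his was the next unopened envelope |
| Screening log (section 8, Rejection log) | Who was screened and included | Envelope number or order, which it is not said to record |
| Testosterone before dosing and at follow-up (section 9, Adherence) | Whether the drug given fits the letter | Whether the letter was meant for that man |
| Independent monitoring (Summary of changes) | That study documents are checked | Any stated check of envelope order |

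The undetected cases are therefore specific: an envelope opened early and then used in its turn, or letters exchanged before they carry a number. In both, all these records would agree with one another.

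**The case against.** The case for the plan is substantial.

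- **Order and timing.** The envelopes follow a numbered sequence with a top-of-the-pile rule. By the scheduled draw the man has consented, been registered and completed his assessments and MRI. In substance he is already committed, and what is missing is a written mark of it. This stands, and it keeps the point modest.
- **Route to bias.** The doctor obtains consent, investigators are blinded, several exclusions rest on measured values, and a doctor assesses the day's results. No section gives the nurse the eligibility decision; she registers the men and takes the blood samples and ECG. This also stands, so foreknowledge has little stated room to act on who enters.
- **A reasoned choice.** Section 9 explains why an unblinded nurse on site was preferred to a pharmacy (short shelf life and transport time). Nothing here disputes that choice.
- **Translation.** The English is a rough rendering of a Swedish text. The place to which the letter returns may be the locked cupboard and not the pile of unused envelopes, so separate filing is a clarification as much as a correction.

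A reader might go further and infer that the assignments cannot be audited, or that a swapped envelope leaves no trace. The records listed above contradict that: use out of order would generally show on reconciliation. A reader might also infer that one slip damages every later assignment, but a randomised list shifted by one place is still randomised.

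**Conclusion.** The point holds as a weakness in concealment from one person and in the audit trail. It does not show that allocation was, or would be, manipulated. Two facts carry it: the allocation is read before any written link to a patient, and the reader is the person who knows all earlier allocations.

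The size of the predictability cannot be fixed from the documents. It runs from 3% to 50% of assignments known with certainty under blocks, if the nurse knows the block size, and from 0 to 2% without blocks. A reader might infer that 15 or 20 of the 60 assignments were known in advance. That follows only for blocks of 6 or 4, with the size known to her, and the documents state neither. Since consent, blinding of investigators and the timing of the draw all limit the harm, this is an improvement worth making because it is cheap, and no reason to doubt the comparison as such.

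**What to change.** Amend sections 7 (Overview design) and 9 (How treatment is assigned) as follows.

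1. Once eligibility is confirmed and baseline is complete, the nurse writes reserve number, date, time and signature on the sealed, lowest-numbered envelope, and only then opens it.
2. Opened envelopes and their letters are filed together, apart from the unopened ones.
3. The existing monitor reconciles envelope order with reserve numbers and dosing times.
4. The list is generated by one stated method without fixed blocks: the urn scheme alone, or randomly varied blocks. Its details are withheld from the site.

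The cost is seconds per patient and a few sentences of text. Dropping fixed blocks may leave the arms slightly unequal. As an assumed example, 27 against 33 gives 1/27 + 1/33 = 0.0673, compared with 2/30 = 0.0667 for equal arms. The ratio is 1.01, so the standard error rises by about 0.5%, which is negligible. For men already randomised, the method and block size can still be stated and the retained letters reconciled, though the missing pre-opening entries cannot be recovered.

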### Blinding and code breaking

The research nurse has training in ICH--GCP and great habit of clinical trials. She is unblinded to the will of the preparatory subject. She documents it in the randomization key stored together with the drugs in a locked cabinet in the drug room at CASM. However, the solution is prepared out of sight for the patient. The subject has a plastic card in a walletformat which says that he is involved in a clinical drug trial but not for which preparation ordiagnosis, it also says which

reserve number person has. According to text on the plastic card, it is asked to contact CASM if necessary for code breaking. Research nurse then calls back and gives information to treating doctors about what substance the patient received. This is then recorded in a fail to note logbook. If it is a serious adverse event, the person is taken out of the study (but is included in intention to treat--analysis). Study participants also have a study diary with info about the study and what to do if any health problems related to the study would occur, as well as where they can write down any side effects.

### Concomitant medication

Not allowed concurrent medications are hormone preparations that affect testosterone levels, or that are at risk of extending QT-interval. The person may not have been involved in any drug study for the past three months, or have used any antiandrogen drugs in the last two years. All other simultaneous treatment is documented in the CRF.

### Adherence

The adherence to treatment is assumed to be complete if the injections could be administered without complications. No drugs should be taken in the home, everything administered on the first day of visits by the research nurse. There is no antidote that the people could take in the home without our knowledge. Vin measures testosterone levels before administration first visit day and on follow-up visits as a marker for antiandrogen effect.

### Drug accounting

Research nurse orders the experimental preparation through ApoEx according to the same procedures as for the other drugs purchased to the clinic. She records receiving drugs in the usual way. Administration is documented in the subject's reserve number journal. Possibly leftover study drugs are saved in the clinic's drug storage room if any other patient after the study's conclusion would need it, in indication according to FASS (advanced prostate cancer).

### Treatment after the end of the study

The subjects are encouraged to enroll as regular patients at CASM after the end of the study, and to present their plastic card with reserve number and information that they have been involved in drug testing. Then the reserve number chart can be linked to the regular charts, still only available within CASM's TakeCare domain, i.e. it is not visible from other clinics. The patient can also discuss with his doctor about the effects of degarelix/placebo and this will be a basis for decisions on whether the patient should continue with antiandrogen therapy. Since the indication pedophilia is currently lacking in degarelix, one of the androgen preparations in the category such as triptorelin (Moapar) or cyproterone acetate (Androcur) are considered.

The effect of degarelix is transient and all patients will regain their regular testosterone levels.

## 10. Assessment of safety and efficacy

### Assessment of clinical effectiveness

The efficacy variables are measured at Karolinska University Hospital Huddinge.

### Assessment of clinical safety

Patients are excluded if on the first day of visits turn out to have:

- ☐ 12-lead-EKG with QT/QTc-interval > 450 ms.
- ☐ Outside reference range on the following samples: Na, K, Creatinine, ASAT, ALAT, gamma-GT, ALP indicating kidney failure or impaired liver function.
- ☐ Osteoporosis Self-Assessment Tool for Men (OST) indicating severe osteoporosis
- ☐ MADRS-S indicating deep depression, or presence of severe suicidal thoughts

Patients are monitored with respect to glucose intolerance and possible diabetes, with the following samples each visit:

- ☐ fB-glucose, hbA1c och fS-insulin

On the first visit, as well as at 2-week- and 10-week follow-up, fB-glucose, hbA1c and fS-insulin, as well as to Na, K, Creatinine, ASAT, ALAT, gamma-GT, ALP.

All samples are labelled for immediate analysis, and the test results are assessed by doctors on the day of the visit so that medical measures can be taken on the same day.

AE/SAE-reporting takes place in cooperation with KTA.

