
### Study drug

Degarelix is a GnRH receptor antagonist. It was approved by the FDA in 2008 for the treatment of patients with advanced prostate cancer (17). It hasn't been tested in pedophilia.

Klotz et al (2008) studied its safety and effectiveness in achieving and maintaining testosterone suppression vis-à-vis leuprolide in a comparative, randomized, open--label, parallel—group phase III study over 1 year on a group of 610 patients with prostate cancer (median age 72 years) (18). Three dosing regimens were compared: the starting dose with 240 mg degarelix subcutaneous in a month, followed by maintenance doses of 80 mg or 160 mg monthly, or 7.5 mg leuprolide. Both intention to treat and per protocol populations were analyzed. Primary endpoint, defined as testosterone suppression at less than 0.5 ng/ml blood on all monthly measurements from day 28 to 364, was achieved at 97.2%, 98.3% and 96.4% of patients, in degarelix 240/80 mg, degarelix 240/160 mg and leuprolide groups (intention to treat--population). 3 days after treatment started, testosterone levels were less than 0.5 ng/ml in 96.1% and 95.5% of patients in the degarelix 240/80 mg and 240/160 mg groups, but not in any in the leuprolide--group. However, the hormonal side effects in the three groups were similar in all three groups. The Degarelix groups (subcutaneous injections) had a higher proportion of skin reactions at the plug-in (40%) compared to those in the intramuscular leuprolide--injection group (0%). Other differences between degarelix vs. leuprolide were the incidence of urinary tract infections (3% versus 9%  $p < 0.01$ ), arthralgia (4% versus 9%,  $p < 0.05$ ) and chills (4% versus 0%,  $p < 0.01$ ). There were no systemic allergic reactions. The authors concluded that degarelix was no worse than leuprolide in maintaining low testosterone levels over a year. Degarelix lowered testosterone levels markedly faster than leuprolide. The median time for testosterone reinhibition was 112 days and the median time to restore testosterone levels was 168 days. The findings in the study of Klotz et al (2008) are supported by studies by Gittelman et al (2008) (19) and Van Poppel et al (2008) (20).

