### Sampling in the study

The following samples will be taken at all three visits, to monitor blood glucose levels, kidney- and liver function, as well as to be able to respond to primary and secondary endpoints.

fB--glucose

hbA1c

fS---insulin

Sodium

Potassium

Creatinine

ASAT

Tool

gamma---GT

ALP

S-testosterone

S---SHBG

S--prolactin

S---oxytocin

S---LH,

S---FSH,

S---Ca,

S--estrogen (sensitive),

S--Prolactin

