## 12. Statistics and data handling

### Data handling

The research data is handled differently depending on the type of information it is.

Personal data, identification key and randomization key are kept in a binder marked PRIOTAB-study under strict secrecy in specially locked cabinets in the drug room at CASM during the time the study runs and 10 years thereafter. It is then destructed. In the same place, the CRF binder is stored with completed interview templates, test results from neuropsychology and self-rating forms.

Lab data is saved in the reserve number chart. It can be linked to the person's regular medical records if he chooses to become a patient at CASM.

MRI data is stored registered on the reserve number in the X-ray clinic's journal system RIS/PACS linked to TakeCare. That data will be burned off on CDs stored in the CRF binder.

When the study is completed, the randomization key is broken and data is transmitted by hand to encrypted file processed in statistical programs.

Quality control of data is done by responsible investigators.

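### Follow-up testosterone, LH and FSH results are filed in the study chart with no stated barrier to blinded staff, and a visible week-2 value would nearly reveal the allocation

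*Supplement*

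**What the plan says.** **Sampling.** Protocol section 6, Sampling in the study, has one list covering glucose, electrolytes, creatinine, liver tests, testosterone, SHBG, LH, FSH, oestrogen and prolactin. It opens: "The following samples will be taken at all three visits". The purpose is safety monitoring "as well as to be able to respond to primary and secondary endpoints". Section 9, Adherence, confirms that the trial measures "testosterone levels before administration first visit day and on follow-up visits as a marker for antiandrogen effect".

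**Reading and storage.** Section 10, Assessment of clinical safety, says: "All samples are labelled for immediate analysis, and the test results are assessed by doctors on the day of the visit". The sentence before it names glucose, HbA1c, insulin, electrolytes, creatinine and liver tests; it begins "On the first visit, as well as at 2-week- and 10-week follow-up, fB-glucose, hbA1c and fS-insulin". Section 12, Data handling, says: "Lab data is saved in the reserve number chart". It makes no exception for hormones.

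**Blinding.** Section 7, Overview design, says: "The investigator and the researchers are also blinded in terms of what substance the research person has been injected". Only the research nurse knows the allocation. Section 12, Statistical analysis, extends blinding to patients, doctors and analysts. The one safeguard it gives is that the group assignment is not disclosed.

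**Expected drug effect.** Section 4, Study drug, reports from the cited phase III trial: "3 days after treatment started, testosterone levels were less than 0.5 ng/ml in 96.1% and 95.5% of patients". The placebo is sodium chloride solution (section 9).

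**The concern.** Degarelix works by suppressing testosterone, so a testosterone result after dosing is close to a statement of the arm. Withholding the assignment protects the blind only if the results that give it away are withheld too. The protocol blinds the doctors, orders these results at the follow-up visits and files them in the study chart, without saying who may open them or when.

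Two things are exposed. The first is adverse-event causality, a matter of judgement graded under Assessment of related links in section 11; adverse events are a secondary endpoint. The second is any week-2 assessment, or conversion of a risk domain to its 0 to 3 score, that is done once the result can be seen. Week 2 is the SAP's time point for the primary analysis. An assessment made with the allocation known cannot be made blind afterwards.

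**Working it through.** The plan gives no figure to reproduce here. The check has two parts: tracing the path of a hormone result, and asking how much one result reveals.

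**Path of a week-2 testosterone result**

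| Step | Where | What is stated | Barrier stated? |
|---|---|---|---|
| Drawn | s. 6 Sampling; s. 9 Adherence | At baseline and follow-up, on the same list as the safety tests | No |
| Timed | s. 7 Assessments and procedures, visit 2 | Blood 8:45–9:15; medical assessment, ratings and adverse-event reporting 9:30–11:00; psychological testing 11:00–12:00 | Turnaround not given |
| Analysed and read | s. 10 Assessment of clinical safety | All samples analysed at once, results read by doctors that day; only safety tests named nearby | No |
| Filed | s. 12 Data handling | Reserve-number chart | No |
| Must not reveal the arm to | s. 7 Overview design; s. 12 Statistical analysis | Investigator, researchers, doctors, analysts | Only non-disclosure of the assignment |

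On the broad reading of the same-day sentence, doctors receive the hormones directly. On the narrow reading, the results still reach the chart with no access rule. The route is open either way; only its directness differs.

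**What one value reveals**

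Inputs:
- Share of degarelix patients below 0.5 ng/ml: s = 0.955 to 0.961 (day 3, section 4). The same section gives 97.2% and 98.3% below that level at every monthly measurement from day 28 to 364, so day 14 lies between two time points with high suppression.
- Share of placebo men below 0.5 ng/ml: f = 0 to 0.05. This is an assumption; the documents give no figure.
- Arm size: 30 (section 12, Study size).

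The rule is to call degarelix if testosterone is below 0.5 ng/ml and placebo otherwise.

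- Expected low values in the degarelix arm: 30 × s = 30 × 0.955 = 28.65, to 30 × 0.961 = 28.83.
- Share classified correctly with equal arms: (s + 1 − f)/2.
- Certainty that a low value means degarelix: s/(s + f).

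| s | f | Classified correctly | Low value means degarelix |
|---|---|---|---|
| 0.955 | 0 | 97.75% | 100% |
| 0.955 | 0.05 | 95.25% | 95.0% |
| 0.961 | 0 | 98.05% | 100% |
| 0.961 | 0.05 | 95.55% | 95.1% |

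With the day-28-onward rates the share classified correctly runs from (0.972 + 1 − 0.05)/2 = 96.1% to (0.983 + 1 − 0)/2 = 99.15%. Guessing without the result gives 50%.

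**Week 10.** Day 70 is a weaker case. The cited trial gave monthly maintenance doses and this trial gives one dose, so its later suppression and recovery figures do not carry over directly.

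**The case against.** The strongest reply is that no sentence says doctors read testosterone. The same-day sentence stands in a safety section, follows a list of safety chemistry, and exists so that medical action can be taken that day. The next section limits the doctor's visit-day review to ECG, the osteoporosis tool, the laboratory samples already listed and the depression scale. Section 9 gives testosterone a different role, as a marker of drug effect. This stands: same-day reading of the hormones by doctors is something a reader might infer, not something the documents state. It does not close the route, because the results still go to the chart without restriction.

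Second, the visit-2 schedule may protect the primary ratings. They start at 9:30 and psychological testing ends at noon, while blood is drawn from 8:45 with no stated turnaround, so the result may well arrive afterwards. This also stands. The exposure is to whatever is assessed, attributed or scored after the result is available. The protocol does not say when, or by whom, the 0 to 3 scores are assigned.

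Third, visit 3 is with the research nurse, who already knows the allocation, so the laboratory result adds little for her.

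Fourth, much of the composite is self-report or neuropsychological testing, which leaves less room for a rater's knowledge to act. This limits the concern for the primary endpoint. It does not help causality grading.

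The statement in section 10 that efficacy responses are compiled only after the study ends does not answer the point. It concerns compiling data, not access to the chart.

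**Conclusion.** The concern holds as a gap in protecting the blind. A near-complete marker of allocation is measured at week 2 and filed where staff who must stay blinded have no stated restriction on seeing it. If seen, it would identify the arm in about 95% to 98% of participants. That figure assumes that day-3 suppression in prostate cancer patients (median age 72) carries over to day 14 in men aged 18 to 65, and that at most 5% of placebo men are below 0.5 ng/ml.

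Three stronger conclusions are tempting, and the documents do not support them:
- That the blind fails. The text leaves it unprotected; it does not show that any blinded person sees a hormone result.
- That the composite is biased by some number of points towards degarelix. The documents give nothing from which to derive a size. Direction is open too: knowing the arm could increase the attribution of adverse events to degarelix.
- That both follow-up visits reveal the arm equally. Only week 2 is well supported; week 10 after a single dose is uncertain.

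This is a cheap improvement that should be made.

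**What to change.** - Split the laboratory order. Send only the safety panel (glucose, HbA1c, insulin, electrolytes, creatinine, liver tests, calcium) to the blinded doctors and the reserve-number chart.
- Hold testosterone, SHBG, LH, FSH, oestrogen and prolactin results outside that chart until database lock. Alternatively, send them only to an unblinded person who does no outcome rating and no adverse-event attribution. The research nurse conducts visit 3, where ratings are scheduled, so she meets that condition only if those tasks are given to someone else.
- State in section 10 that outcome raters, those who assign the 0 to 3 scores, and adverse-event assessors have no access to hormone results, and that the same-day review covers the safety panel only.

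The cost is a changed requisition, a separate reporting route and a few sentences of protocol. The blood samples stay the same, and the safety chemistry still reaches the doctors on the visit day. The downside is that the blinded doctor does not have hormone values in real time; the existing code-break procedure in section 9 remains available.
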